## **TMS measures analysis**

Corticospinal plasticity will be determined through changes of the corticospinal excitability and the central motor conduction time. Hence, we will quantify bilateral rMT, MEP amplitude and latency, because each measure can assess different plastic changes across the neuromotor axis and they can be used as a proxy of corticospinal plasticity. Resting motor threshold (% maximum stimulator output) states the general excitability of the neuromotor axis in the target muscle,

amplitude (mV) expresses transynaptic activation of corticospinal neurons (78), while latency (ms) is the time between the TMS onset and the MEP onset, which refers to the integrity of the white matter fibers (79).

For both upper limbs, all neurophysiological measures (i.e., rMT, MEP amplitude, latency) will be first calculated from each MEP trace and then averaged to get a single value. These calculations will be done according to the different time points for each participant in the baseline phase, at five time points in the intervention phase and at three time points in the follow-up phase (see Figure 1). In order to investigate possible changes in cortical excitability, we will measure rMT and peak-to-peak amplitude throughout assessing MEPs (80) of the Abductor Pollicis Brevis muscle, while measuring of latency will indicate possible changes in CMCT. Any changes in all measures across time points, will indicate alterations in corticospinal plasticity (81). We will evaluate resting motor threshold using MTAT 2.0 (64) (available at <http://clinicalresearcher.org/software.htm>) and to investigate possible changes in individual corticospinal plasticity of each participant, we will calculate bilaterally the difference between the mean values of each phase (82,83). On the other hand, from each stimulus response during the suprathreshold stimulation (i.e., 120% of rMT) (81), we will calculate offline the MEP peak-to-peak amplitude and latency. To define CMCT (ms), we will subtract the peripheral conduction time ((F wave latency + M wave latency – 1)/2) from the CMCT (MEP latency). The F wave is the muscle response elicited by activation of the alpha motor neuron, while the M wave is the direct response of the muscle (84). A prolonged CMCT indicates damage of large fibres, demyelination of central motor pathways or slow summation of descending excitatory potentials in the corticospinal tract evoked by TMS (84,85). To standardise all latencies (i.e., MEP, F and M wave), we will use a visual inspection from stimulation onset to response onset, performed from the same investigator so to ensure reliability of the study across all time points. To define possible changes in CMCT, we will evaluate bilaterally the difference between the mean values of each phase.

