### **Data Acquisition of Outcome Measures**

#### **Primary Outcome Measures**

We will assess the corticospinal plasticity using single pulse TMS in the neurophysiology lab of the Cyprus Institute of Neurology and Genetics, in all phases (see Figure 1). Using electromyography (EMG) signals, we will analyze bilateral cortical excitability and bilateral CMCT

to determine corticospinal plasticity and therefore to test the primary hypothesis. The rMT and the MEP amplitude of Abductor Pollicis Brevis muscle will define cortical excitability, while we will use the MEP latency to calculate the CMCT. During all neurophysiological assessments, participants will be in a relaxed sitting position in a comfortable chair with feet touching the floor and both arms will be placed on cushioned armrests and with the head rested on a cushion. To ensure methodological consistency, we will collect all data by performing the same methodological procedures for both conditions (i.e., cortical excitability and CMCT) bilaterally (one side per assessment), across participants and across all time points.

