### **Isometric Dynamometer**

The isometric muscle force of the major muscle groups will be assessed with the use of the muscle controller (Kinvent Biomechanique, Montpellier, France), which is a dynamometer used in the evaluation and rehabilitation of muscle strength that provides real time biofeedback. The patient lies (supine or prone) on a therapeutic bed and the physiotherapist, with the use of the muscle controller, holds against the patient's limb as the patient exerts a maximal force. The physiotherapist counters the force (make test), or tries to break the contraction (break test) and the data will be collected and stored using the KFORCE APP (Kinvent Biomechanique, Montpellier, France). Shoulder flexors, extensors, rotators, horizontal adductors and abductors, adductors and abductors, elbow flexors and extensors are the major muscle groups which will be evaluated (73). ). Shoulder flexors, extensors, rotators, horizontal adductors and abductors adductors and abductors, elbow flexors and extensors are the major muscle groups which will be evaluated. A separate value for each muscle group will be recorded in order to be used in the visual and statistical analysis.

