### **Statistical analysis**

For each of the outcome variables that the visual analysis indicates a potential functional effect, a quantitative analysis will be performed to estimate the effect size. This analysis will be performed for each variable at which a significant trend is shown as described in the previous section. In order to estimate the individual-level effect sizes, we will use three different methods, as suggested by 'What Works Clearinghouse' (50), the standardized mean difference (Cohen's  $d$ ), the standardized mean difference with correction for small sample sizes (Hedges'  $g$ ) and piecewise regression analysis which does not only reflect the immediate intervention effect, but also the intervention effect across time. Multilevel modelling, which is recommended by the 'What Works Clearinghouse' and the single case educational design, specific mean difference index will be used to estimate the magnitude of the effect across cases and compared to the effect obtained by the single level estimates (77). For all the different neurophysiological parameters and clinical conditions, evaluated separately, the null hypothesis is that "there is no improvement from the proposed intervention", thus participants' responses are independent from the condition (baseline versus intervention) under which they were observed. The alternative hypothesis is that "the neurophysiological parameters and /or the clinical condition of the participants will be affected by the specific intervention", again assessed separately. We will reject the null hypothesis if the  $p$  value is smaller than 0.05. All tests will be two sided. Statistical analyses will be performed using the statistical software R (<https://www.r-project.org/>).

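### Six unranked primary TMS measures are each tested at two-sided 0.05 without adjustment, and the statement of what counts as a plasticity change is ambiguous and has no direction

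*Protocol*

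**What the plan says.** Under *Primary Outcome Measures* the protocol says that "we will analyze bilateral cortical excitability and bilateral CMCT", and that this is done "to determine corticospinal plasticity and therefore to test the primary hypothesis". Excitability has two components: "The rMT and the MEP amplitude of Abductor Pollicis Brevis muscle will define cortical excitability". CMCT is derived from MEP latency. No measure or side is named as leading, and nothing says how many measures must change.

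*TMS measures analysis* says "we will quantify bilateral rMT, MEP amplitude and latency", and later adds: "Any changes in all measures across time points, will indicate alterations in corticospinal plasticity". The same section reads a prolonged CMCT as a sign of fibre damage, demyelination or slowed summation. *Participants and methods* lists a possible fall in CMCT among the expected results.

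*Statistical analysis* evaluates each parameter separately. The null opens as "there is no improvement from the proposed intervention". The same sentence then restates it as responses not depending on the phase in which they were observed. The alternative is that the parameters are affected. Rejection is at a p value below 0.05, and "All tests will be two sided". No multiplicity adjustment is stated.

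*Analysis plan* and *Statistical analysis* limit the quantitative step to variables for which the visual analysis suggests a functional effect.

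**The concern.** One primary hypothesis is attached to several measures. Each can be rejected alone at the full 0.05, and no rule says how the separate results combine into a single answer. If one rejection among six is enough, the chance of a false claim about corticospinal plasticity in a subgroup exceeds the 5% that a reader would assume from the stated threshold.

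The wording adds to the problem. The interpretive sentence accepts a change of any size and in either direction, and it does not make clear whether one measure or every measure must change. The null mixes a directional phrase with a non-directional restatement and a two-sided test. At stake is whether a reported alteration in plasticity can be told apart from chance, and whether it can be told apart from a worsening.

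**Working it through.** **Inputs.** Three measures (rMT, MEP amplitude, CMCT) on two sides, from *Primary Outcome Measures*. Threshold 0.05, two-sided, one null per parameter, from *Statistical analysis*. The protocol gives no correlation between measures or sides, so a range is assumed. One p value per measure is counted.

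**1. Number of primary measures.** 3 × 2 = 6. The protocol does not state this count. If MEP latency and CMCT are both counted, it is 4 × 2 = 8.

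**2. The plan's own figure.** One test: 1 − 0.95 = 5%. No family-wise rate and no power are stated, so there is nothing further to reproduce.

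**3. Six tests, independent, without the visual screen.** 1 − 0.95^6 = 1 − 0.735 = 26.5%. With eight: 1 − 0.95^8 = 33.7%.

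**4. Correlated measures.** Simulation of equally correlated normal statistics, two-sided, no true effect, 400,000 draws per setting:

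| Assumed correlation | 6 measures, 0.05 each | 8 measures, 0.05 each | 6 measures, 0.05/6 each |
|---|---|---|---|
| 0 | 26.5% | 33.6% | 4.9% |
| 0.3 | 24.1% | 30.0% | 4.7% |
| 0.5 | 20.7% | 25.1% | 4.1% |
| 0.8 | 13.8% | 15.7% | 2.8% |
| 0.9 | 10.8% | 11.9% | 2.1% |

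The last column uses 0.05/6 = 0.0083. This is also Holm's first step, so it gives Holm's chance of any rejection when nothing has an effect.

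**5. Only improvement counts.** A two-sided 0.05 test spends 0.025 in the favourable direction: 1 − 0.975^6 = 14.1% under independence.

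**6. The visual screen.** A measure is rejected only if it passes the screen and then has p < 0.05. For a fixed test, the screen can therefore only lower the rates in steps 3 to 5. By how much cannot be calculated. *Visual analysis* names six features and gives a numerical cut-off for stability, but no rule for combining the features into pass or fail. The screen also looks at the same data points as the test and favours variables that already appear changed, so a later p < 0.05 is not an independent check.

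**7. The wording, side by side.**
- Interpretive sentence: any change, no size or direction, and either one measure or all of them. Same section: prolonged CMCT indicates damage. Expected results: CMCT falls. A lengthening would satisfy the sentence and contradict the other two statements.
- Null: the opening phrase is directional. The restatement (no dependence on phase), the alternative (affected) and the two-sided test are not.

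**The case against.** Much can be said in the plan's defence.

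- **The screen.** Not every measure is tested. This stands: the percentages describe tests without the screen, and it cannot be inferred that the plan will very probably declare a false effect. The screen still does not control error, for the reasons in step 6.
- **The interpretive sentence.** It may only explain what the measures reflect, with rejection defined elsewhere. If every measure had to change, the chance of a false joint claim could not exceed that of a single test, 5%. This reading is possible. The separate evaluation in *Statistical analysis* favours the other one, and the protocol should not leave the choice open.
- **Sidedness.** The restated null and the alternative both fit a two-sided test. This stands: the defect is one inconsistent phrase, and alpha need not change.
- **Deterioration.** A reader might infer that a worsening would be reported as success. The documents do not support that: the expected results, the Improvement Rate Difference and the closing lines of *Visual analysis* all look for improvement. What is missing is a stated favourable direction for rMT and MEP amplitude.
- **Pooling.** A reader might multiply up to six subgroups, 1 − 0.95^36 = 84%. *Study design* treats each subgroup of five as its own study and plans no claim across them, so the subgroup is the right family. Adding the secondary outcomes is tempting too, since for strength "A separate value for each muscle group will be recorded in order to be used in the visual and statistical analysis". Whether each muscle group is also counted by side is not clear, and those outcomes do not carry the primary hypothesis.
- **Left to the SAP.** An adjustment method often is. Here, however, the protocol itself states the rejection rule for each variable.
- **Several measures are deliberate.** The protocol says each captures a different plastic change, and its aim is bilateral. This stands, and the fix keeps all six. Choosing one side-averaged primary measure would be a trade-off that the point does not need.

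**Conclusion.** The point holds within one subgroup. Six unranked primary measures, each rejected at 0.05 without adjustment, do not give a 5% error rate for the primary hypothesis when any one of them can carry it. Without the screen, the illustrated rate runs from 26% (independent) through about 21% (correlation 0.5) to about 11% (correlation 0.9), and is 14% under independence if only improvement counts. These figures assume equal correlations, one valid p value per measure and no effect of the screen. The true rate under the plan may be lower and cannot be derived from the protocol. If every measure must change, the inflation disappears, but the protocol does not say so.

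The missing direction and the mismatched null are defects of wording. They matter because they leave the protocol without a clear statement of which result would support its hypothesis.

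**What to change.** 1. In *Statistical analysis*, apply Holm across the six primary TMS measures within each subgroup: the smallest p value against 0.05/6 = 0.0083, the next against 0.05/5 = 0.01, and so on up to 0.05. Count a measure that fails the visual screen as not rejected, and keep six as the number in the adjustment. The screen then cannot shrink the family after the data have been seen.
2. In *TMS measures analysis*, replace the interpretive sentence with a favourable direction per measure: lower rMT, larger MEP amplitude, shorter CMCT. Only the CMCT direction is explicit in the protocol; the investigators should confirm the other two.
3. State the null as no change between phases, keep the two-sided test, and claim improvement only when the adjusted test rejects and the estimate lies in the favourable direction.

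The cost is a revision of two sections and a stricter threshold, with fewer nominally significant results. No extra participants, visits or measurements are needed.

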### **TMS assessment**

Following TMS recommended guidelines concerning safety and experimental conditions (59,60), we will assess bilateral cortical excitability and bilateral CMCT. We will apply TMS single pulses (61) via figure-eight coil (C-B60; inner diameter: 35mm, outer diameter: 75mm), connected to the MagPro R20 (MagVenture User Guide, United Kingdom edition, MagVenture A/S, Denmark). For the TMS procedures, we will first find the optimal stimulation site (i.e., hot-spot), next we will determine the rMT, and then apply a bout of single pulses using suprathreshold stimulation. To determine hot-spot (i.e., the spot in which the largest response of the target muscle is elicited), we will deliver single pulses at low intensities (e.g., ~20% maximum stimulator output) and gradually increase it by 5%, maximum stimulator output until we will reach the intensity that will elicit three consecutive MEPs with peak-to-peak amplitude greater than 50mV (62,63). Then, we will determine the rMT of the target muscle which is the minimum stimulation intensity needed to produce MEPs of the target muscle and it is defined by the hot-spot. To identify the rMT of the Abductor Pollicis Brevis muscle, we will employ an adaptive threshold-hunting method, the Motor Threshold Assessment Tool (MTAT 2.0) (64) (available at <http://clinicalresearcher.org/software.htm>). The specific method has the advantage of speed without losing accuracy when compared to the relative-frequency methods based on the Rossini–Rothwell, although both methods have similar precision (65). Then, to quantify the MEP-derived measures of interest (i.e., MEP amplitude, latency), we will apply 25 suprathreshold stimuli (66) at 120% of the rMT (67).

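### The CMCT formula is circular as written, raw MEP latency is also read as central conduction, and the TMS session has no step for recording the F and M waves the formula needs

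*Protocol*

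**What the plan says.** All references are to the Protocol.

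- **Participants and methods** lists three TMS measures of corticospinal plasticity: rMT, MEP amplitude and CMCT.
- **Primary Outcome Measures** treats MEP latency as an input to CMCT: "while we will use the MEP latency to calculate the CMCT". It also asks for identical procedures for excitability and CMCT across participants and time points.
- **TMS measures analysis** opens with excitability and CMCT as the determinants of plasticity, but then quantifies rMT, amplitude and latency. It interprets latency directly: "latency (ms) is the time between the TMS onset and the MEP onset, which refers to the integrity of the white matter fibers (79". Its list of measures leaves CMCT out: "all neurophysiological measures (i.e., rMT, MEP amplitude, latency) will be first calculated from each MEP trace and then averaged". It adds "while measuring of latency will indicate possible changes in CMCT", and says that a change in any of the measures over time points to altered corticospinal plasticity.
- The same section then defines CMCT: "we will subtract the peripheral conduction time ((F wave latency + M wave latency – 1)/2) from the CMCT (MEP latency". It plans to read MEP, F and M latencies by eye, with one investigator doing so at every time point, and to compare CMCT between phase means.
- **TMS assessment** sets out the session: "we will first find the optimal stimulation site (i.e., hot-spot), next we will determine the rMT, and then apply a bout of single pulses". It goes on to 25 stimuli at 120% of rMT. It describes no recording of F or M waves.

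**The concern.** Three things go wrong in the specification of one primary measure.

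First, the only formula for CMCT names CMCT as the quantity from which peripheral time is subtracted. The reader has to repair it.

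Second, two quantities carry one interpretation. MEP latency runs from the cortical stimulus to the muscle response, so it includes peripheral conduction. The protocol concedes this by subtracting a peripheral time to obtain CMCT. Yet raw latency is also tied to white-matter integrity and to CMCT change, and it falls under the rule that any change means plasticity. A shift that arises wholly in the periphery would satisfy that rule.

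Third, the formula needs F and M latencies at every time point, while the detailed session procedure gives no step that produces them. They cannot be taken from MEP traces, which are responses to cortical stimulation. A recording that is not made at a baseline session cannot be recovered later.

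**Working it through.** The protocol states no latency values, variances or effect sizes for these measures, so there is no figure to reproduce. The check is algebraic, on assumed latencies that are not in the document: MEP 20, 24, 28, 32 ms; F 25, 28, 31 ms; M 3, 4, 5 ms, giving 4 × 3 × 3 = 36 combinations.

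**Step 1. Peripheral conduction time (PCT).** The protocol's expression is PCT = (F + M − 1)/2.
- Lowest: (25 + 3 − 1)/2 = 13.5 ms.
- Highest: (31 + 5 − 1)/2 = 17.5 ms.

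**Step 2. Two readings of the CMCT sentence.**
- Intended, CMCT = MEP latency − PCT: from 20 − 17.5 = 2.5 ms to 32 − 13.5 = 18.5 ms.
- Literal, CMCT − PCT, so that peripheral time comes off twice: from 2.5 − 17.5 = −15.0 ms to 18.5 − 13.5 = +5.0 ms. It is negative in 28 of the 36 combinations.
- Example, MEP 24, F 28, M 4: PCT = (28 + 4 − 1)/2 = 15.5 ms; intended 24 − 15.5 = 8.5 ms; literal 8.5 − 15.5 = −7.0 ms.

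The literal reading mostly gives impossible times. It is a drafting error, not a usable alternative definition.

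**Step 3. A purely peripheral change.** Let peripheral conduction slow by 1 ms each way. The F wave travels the segment twice, so F goes from 28 to 30 ms; M is held at 4 ms; MEP latency goes from 24 to 25 ms.
- PCT: (30 + 4 − 1)/2 = 16.5 ms, a change of 1.0 ms.
- CMCT: 25 − 16.5 = 8.5 ms, a change of 0.0 ms.
- MEP latency: a change of 1.0 ms.

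Under the protocol's rule the latency change counts as plasticity; the correctly computed CMCT shows none.

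**Step 4. Which quantity is judged.** The Visual analysis section assesses stability by the share of points within 15% of the phase median. In the same example the band is 0.15 × 24 = 3.6 ms for MEP latency and 0.15 × 8.5 = 1.275 ms for CMCT. Stability is one of six visual features, and the visual analysis decides whether a quantitative analysis follows, so the choice of quantity has to be fixed.

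**Step 5. Acquisition.** The TMS assessment section, TMS measures analysis and the formula do not join up. The session produces a hot-spot, an rMT and 25 MEPs. The formula needs MEP, F and M latencies. The F and M inputs have a reading rule but no recording step.

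**The case against.** The best defence is that the meaning is clear. The bracket names MEP latency, the Primary Outcome Measures section makes latency an input to CMCT, and CMCT has its own between-phase comparison. This stands. A reader might infer that the primary measures fail to remove the peripheral signal; for CMCT that is not supported, because the intended formula removes it, as Step 3 shows.

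A reader might also infer that F and M waves are never recorded and that CMCT cannot be derived. The text does not support that either: F and M latencies are to be read at all time points. What is missing is the description of how they are acquired.

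It might be argued that using MEP latency dilutes a central effect because CMCT is only part of it. That does not follow for the planned comparisons. A 1 ms central change is 1 ms in both quantities, and the plan compares phase means and standardized differences. The standardized size depends on within-phase variability, which the document does not give, and CMCT also carries the reading error of F and M.

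Finally, MEP amplitude in raw mV might look like the same fault. It contradicts nothing in the protocol. Comparisons are within participant, and the formula calls only for M-wave latency, not for a maximal M-wave amplitude.

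The defence does not reach the wording that reads raw latency as central conduction and any change as plasticity, nor the gap in the session procedure.

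**Conclusion.** The point holds in three parts: the CMCT definition is circular as written; raw MEP latency is given a central interpretation that it cannot carry alone; and the TMS session does not describe the F- and M-wave recording that a primary measure depends on. The practical size is that a peripheral shift passes in full into MEP latency (1.0 ms per 1 ms) and not at all into correctly calculated CMCT (0.0 ms). That result follows from the formula; the particular latencies are assumed, and the example takes the slowing to affect the F wave in both directions with M unchanged. How often or how far peripheral conduction would shift in these participants cannot be judged from the document. The intended CMCT analysis is sound once the sentence is corrected, so this is a limited repair and not a reason to discard the measure.

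**What to change.** 1. In TMS measures analysis, replace the defining sentence with: CMCT = MEP latency − (F latency + M latency − 1)/2.
2. Name CMCT as the central-conduction outcome in every list of TMS measures. Delete the statements that raw MEP latency indicates CMCT change or, by itself, plasticity. Report MEP latency only as a component of CMCT, and exempt it from the rule that any change counts as plasticity.
3. In TMS assessment, add the F- and M-wave recording that the formula presupposes, on the same side and in the same session as the MEPs, at every time point.

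The first two changes cost only wording. The third makes explicit a recording that the formula already requires; any extra session time comes from that existing requirement. Relating MEP amplitude to the M wave could be offered as an optional sensitivity analysis, but it would need a maximal M-wave amplitude that the protocol does not now ask for, and it is not part of the correction.

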### **Secondary outcome measures**

All clinical assessments will be performed in all phases (see Figure 1) in the physiotherapy unit of the CING and reliability of the measures will be assessed by having two trained physiotherapists, blinded to the research study, independently record the measures of each outcome.

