## **Modified Fatigue Impact Scale (MFIS)**

It is a short questionnaire which requires the participants to describe the effects of fatigue during the past four weeks (75). The MFIS consists of 21 questions which are subjectively rated from "0" (low rate) to "4" (high rate) and it is also divided into three subscales (i.e., physical, cognitive, and psychosocial). The higher the score is, the greater is the impact of fatigue in individual daily life. Although, to describe fatigue level the Fatigue Severity Scale is more commonly used, we decided not use it because it describes severe fatigue. Therefore, we will use the Modified Fatigue Impact Scale as the description of participants' attribution of functional restrictions to fatigue symptoms.

The intervention protocol and all clinical assessments will be performed in the physiotherapy unit of the CING and reliability of the measures will be assessed by having two trained physiotherapists, blinded to the research study, independently record the measures of each outcome. Also, neurophysiological assessments will be executed and recorded from the experimenters who are trained in the use of the TMS equipment regarding the needs of the proposed study, in the neurophysiology lab of the CING, in separate days from those of the clinical assessments. During the follow-up phase both clinical and neurophysiological assessments will be performed at the same day for each participant. To note, each participant has to complete at least 27 (75%) out of 36 sessions in order to be included in the final data analysis (76). All of the measures are to be administered by the clinical research team member (senior physiotherapist) under the supervision of the project coordinator. All data and personal information collected from the study will be stored safely without being shared between researchers at the premises of CUT and CING. Five years after data collection the measurements and records will be safely destroyed.

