### **Visual analysis**

Two assessors will systematically measure each outcome measure across time, inter-assessor agreement will be calculated on at least twenty percent of the data points in each condition. The minimum acceptable inter-assessor agreement will be set to 0.8 (50). Initially, a visual analysis will be conducted and presented graphically in a spaghetti plot, in order to define whether there is a functional relation between the intervention and the outcome measures (77). During the visual analysis, six features of the research design graphed data will be examined: level, trend, stability, immediacy of the effect, overlap, and consistency. Over the within-phase examination an evaluation of level, trend and stability will be examined. Level will be reported from the mean score of each dependent variable and trend will determine whether the data points

are monotonically decreased or increased. Stability will be estimated based on the percentage of data points falling within 15% of the phase median, if this is higher than 80% then we assume that this criterion is met. Additionally, over the between-phase examination an evaluation of overlapping data among baseline and intervention phases, consistency of data patterns and immediacy of effect will be performed (77). The Percentage of Non-overlapping Data index will be used to quantify the proportion of data points in the intervention phase that do not overlap with the baseline phase (86) and the test statistic will be calculated using the Improvement Rate Difference as an effect size index. Immediacy of the effect will be examined by comparing changes in level between the last three data points of one phase and the three first data points of the next phase. Furthermore, consistency of data patterns involves the observation of the data from all phases within the same condition, with greater consistency expressing greater causal relation. Each feature will be assessed individually and collectively across to all participants and to all phases. Consequently, if the intervention protocol is the sole determinant of improvement, we expect to find indicators of improvement only at the intervention phase.

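### The latencies behind the primary CMCT outcome are marked by eye by one investigator with no stated masking to phase, and the plan's own two-assessor rule is not met for them as worded

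*Protocol*

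**What the plan says.** Under Primary Outcome Measures, the protocol analyses cortical excitability and CMCT on both sides "to determine corticospinal plasticity and therefore to test the primary hypothesis". For CMCT it states: "we will use the MEP latency to calculate the CMCT". The formula is in TMS measures analysis: "we will subtract the peripheral conduction time ((F wave latency + M wave latency – 1)/2) from the CMCT (MEP latency". I read this as MEP latency minus peripheral conduction time.

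The same section describes how the MEP, F-wave and M-wave latencies are obtained: "we will use a visual inspection from stimulation onset to response onset, performed from the same investigator so to ensure reliability of the study". It says that MEP latency is derived offline, and it defines the effect as follows: "To define possible changes in CMCT, we will evaluate bilaterally the difference between the mean values of each phase".

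The Visual analysis section sets a general rule: "Two assessors will systematically measure each outcome measure across time, inter-assessor agreement will be calculated on at least twenty percent of the data points". The rule applies in each condition, with a minimum acceptable agreement of 0.8, and no outcome is exempted.

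On who performs the TMS work, the closing paragraph of the MFIS section says only that experimenters trained on the equipment carry out and record the assessments. No section says whether the latency reader is masked to phase, date or participant.

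**The concern.** Marking an onset by eye is a judgement. The protocol relies on one reader for consistency, which removes differences between readers. It does not protect against a reader whose marking changes with what is expected of the phase. The direction is stated in advance: the expected results in Participants and methods include a possible reduction of CMCT.

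The design makes this kind of error hard to recognise. Staggered baselines guard against calendar-time drift, but an expectation that changes when each participant enters intervention follows the stagger. It could produce change only in treated participants and consistently across them, which is the pattern that Study design and Visual analysis treat as evidence of cause. Averaging over the 25 stimuli reduces random marking error, not a directional one. The same readings also decide whether the quantitative analysis is run and then supply its estimate.

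The two-assessor rule would give some check on the readings, but as written it has nothing to operate on for CMCT.

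**Working it through.** The protocol gives no error or precision figure for latency marking, so there is no stated figure to reproduce. The check compares the texts and then works through the protocol's own formula.

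**1. The two rules side by side**

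| Item | TMS measures analysis | Visual analysis |
|---|---|---|
| Readers | one investigator for MEP, F and M latencies | two assessors for every outcome measure |
| Points read twice | none stated | at least 20% in each condition |
| Agreement criterion | none stated | minimum 0.8 |
| Masking to phase | not stated | not stated |

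With one reader, no points are read twice and the 0.8 criterion cannot be evaluated for CMCT.

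**2. How a marking shift reaches CMCT**

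CMCT = L_MEP − (L_F + L_M − 1)/2. The sensitivities are 1 for MEP and −0.5 each for F and M.

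Let b be a shift present in one phase and absent in the other. The value b = 0.5 ms is assumed; the protocol gives none.

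- Same shift on all three waves: b − (b + b)/2 = 0 ms.
- MEP only: b = 0.5 ms.
- MEP one way, F and M the other: b + b/2 + b/2 = 0.5 + 0.25 + 0.25 = 1.0 ms.

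For any assumed b the range is 0 to 2b.

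**3. Which shifts matter**

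The effect is a difference of phase means. A shift that is the same in both phases gives (mean₂ + shift) − (mean₁ + shift) = mean₂ − mean₁, so it drops out. Only the part that differs between phases enters the effect.

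**4. Random marking error, for comparison**

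Independent errors of SD s on each wave give a CMCT error SD of s × √(1 + 0.25 + 0.25) = 1.22 s. Averaging reduces this component, but not the one in step 2.

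**5. What the 20% rule would require**

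The protocol gives five intervention and three follow-up assessments per participant, and five participants per subgroup. I read condition as phase. Per limb:

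- Intervention: 5 × 5 = 25 points, at least 0.20 × 25 = 5 read twice.
- Follow-up: 5 × 3 = 15 points, at least 0.20 × 15 = 3 read twice.
- All 30 participants: at least 30 of 150 and at least 18 of 90.

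The baseline number depends on Figure 1, which is not shown, so it is not computed.

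**The case against.** The best defence is that silence is not evidence of an unmasked reader. The protocol does not say how traces are labelled when read offline, and coding details could sit in an analysis plan or laboratory procedure not shown. That stands: a reader might infer that the investigator sees participant and phase, but the text does not say so. The use of ID numbers instead of names does not settle it either way, since an ID does not hide phase. What the protocol itself fixes is the single reader alongside a two-assessor rule, and that needs correcting whatever other documents exist.

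It can also be said that naming one investigator for consistency does not exclude a second person re-reading a sample. That is true, and the sections can be reconciled in a sentence or two. The protocol does not contain them.

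Two stronger readings are tempting and go too far.

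- A reader might infer that the plan breaks its own blinding rule. The clinical outcomes are recorded by "two trained physiotherapists, blinded to the research study, independently record the measures of each outcome". That covers the clinical measures only and does not mention phase. It is a safeguard that the latencies lack, not a rule that the latency reading violates.
- A reader might infer that this clinical blinding is itself contradicted by "All of the measures are to be administered by the clinical research team member (senior physiotherapist) under the supervision of the project coordinator". One person can administer a test while two others record it, so this is not a strict contradiction and forms no part of the point.

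**Conclusion.** The point holds in a limited form. For a primary outcome, the protocol has one investigator mark all three latencies by eye, states no masking to phase, and does not meet its own requirement for two assessors and an agreement figure. This should be corrected before any latency is read.

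The possible bias is 0 to 1.0 ms in the CMCT phase difference, if marking shifts by 0.5 ms between phases. The 0.5 ms is an assumption, and 1.0 ms is the worst case, not an expected value. The protocol gives neither an expected CMCT change nor its variability, so the size cannot be set against the effect sought, and nothing shows that such a shift would occur.

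The finding does not extend to the whole primary set. rMT is obtained with the adaptive threshold-hunting tool MTAT 2.0, and the sentence on marking by eye concerns latencies, not MEP amplitude.

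**What to change.** Amend TMS measures analysis as follows, and refer to it from Visual analysis:

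1. Check trace quality at the session, so that unusable MEP, F or M recordings are noticed in time.
2. Once a participant's series is complete, export the traces under random codes, shuffled over phases and dates within that participant. Alternatively, shuffle over the whole subgroup once all five series are complete.
3. Have the same investigator mark all onsets, masked to phase. This keeps the consistency the protocol wants.
4. Have a second, already trained TMS experimenter re-read at least 20% of data points per phase, also masked, and report agreement against 0.8. Masking both readers matters because two unmasked readers could share the same expectation and still agree.

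The cost is a short relabelling step and some re-reading time by existing staff, with no new visits or equipment. The drawback is that latencies are not available until the participant's series is complete, or until the last of the five participants finishes if shuffling covers the subgroup.
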